#### Secondary analysis

Secondary outcomes will be similarly modelled based on the form of the dependent variable. Binary and count outcomes will be modelled using binomial and Poisson GLMMs, respectively. Models for count outcomes will assume a common denominator of cases per 1000 surgeries. Length of stay will be modelled using Cox proportional hazards regression. Analysis of survey and activity log data will be reported descriptively by study period.

Results for intention-to-treat (ie, all data analysed for all sites as randomised) and per-protocol (ie, data will be censored for sites if they withdraw from the trial protocol) will be reported. Missing data on primary and secondary outcomes is expected to be low. In the event of missing data on patient-level covariates, missingness will be investigated and if missing at random variables will be imputed using multiple imputation. Levels of missing data (if any) will be reported in planned research outputs.

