### Outcome measures

Table 1 presents primary, secondary and other outcomes including measurement variables and time points.

**Table 1 T1:** Outcome evaluation

	Outcome variable	Measure
Clinical effectiveness outcomes		
1	Perioperative hypothermia on post anaesthetic care unit (PACU) arrival	Body temperature <36°C recorded within 15 min of PACU arrival time
2	Perioperative hypothermia at any time point	Body temperature <36°C at any time point: (1) within hour prior to surgery; (2) on induction; (3) intraoperatively; (4) during PACU admission; (5) on ready to discharge from PACU
3	Hospital length of stay	Days of separation (hospital)
4	PACU length of stay	Minutes (from PACU admission to discharge)
5	Intraoperative events	Complications recorded during the surgical episode
6	PACU events	Complications recorded during PACU admission
7	Blood product transfusions	Number of units transfused in surgery and PACU
8	Surgical site infection (SSI)	SSI at time point: (1) on hospital discharge; (2) postoperative day 30 at hospital visit (superficial incisional/deep incisional/organ or space SSI), or by Bluebelle self-report wound healing validated survey^31^
Implementation outcomes		
Anticipated		
9	Implementability:appropriateness, acceptability, feasibility^32^	Pre and post implementation survey:(1) Acceptability of Intervention Measure; (2) Intervention Appropriateness Measure; (3) Feasibility of Intervention Measure^34^
10	Adoptability:intention to use^32^	Pre and post implementation survey:Adapted Clinicians’ Assessments of Practice Guidelines in Oncology tool^33^
11	Implementation readiness	Pre and post implementation survey:Organisational Readiness to Change^35^
Actual		
12	Implementation and sustainment: extent the simple principles and recommendations are being enacted^32^	Process of care audit of:Temperature monitoring: (1) preoperatively; (2) before induction; (3) intraoperatively; (4) in PACUActive warming: (1) preoperatively; (2) intraoperatively; (3) in PACU
13	Adoption: extent that teams decide to put the simple principles and recommendations in place^32^	Post implementation site survey
14	Fidelity of trial implementation strategy	Site implementation team meeting notes and activity log: trial implementation strategy, practice change initiatives, team attendance

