### Data analysis

#### Sample size determination and power

As recommended by Curran *et al*^41^ we have selected one co-primary aim in determining the required sample size: the clinical effectiveness outcome of perioperative hypothermia (table 1). The expected proportion of patients with perioperative hypothermia on PACU arrival at baseline is 0.274 (27%), based on a recent period prevalence study of five Australian hospitals.^2^ Minimum sample sizes were calculated based on the primary clinical outcome assuming unequal cluster sizes using a constrained randomisation approach.^29 30^ The use of constrained randomisation allows for site-specific sample sizes to represent a fixed proportion of their total surgical capacity, while aiming to minimise imbalance between the total sample sizes for control and intervention periods. For each month a site is in the control or intervention period, we will select a random sample of patients equal to 10% of monthly surgical cases, stratified according to the duration of surgery. Based on annual surgical numbers for participating sites, a 10% sample corresponds to 59–226 patients/site/month. To obtain at least 80% power, our proposed sampling strategy will detect a statistically significant and clinically relevant reduction from 0.274 (27%) in the control period to 0.2 (20%) in the intervention period. Calculations assume a 5% level of statistical significance, an expected intraclass correlation coefficient of 0.1. Across the constrained subset of possible randomisations, the total sample size for control and intervention periods combined will be between 12 732 and 14 100.

For the sample size, we have also considered the minimum detected increase in the primary implementation outcome. Given the lack of existing data on both monitoring and warming recommendations, we have used data on adherence to perioperative temperature monitoring at all recommended time points.^2^ Assuming that 2.7% of patients currently receive temperature monitoring at all recommended time points, with remaining parameters unchanged, we will be able to detect an increase from 0.027 (2.7%) in the control period to 0.1 (10%) in the intervention period with 82% power.

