#### Primary analysis

The co-primary outcomes will be analysed using generalised linear mixed models (GLMM), assuming binary dependent variables. A random intercept will be defined for each site to account for clustering of observations under the stepped wedge design. Fixed effects will include intervention exposure (yes/no), calendar time to account for secular trends unrelated to the intervention (in months)^21^ and patient-level/surgery-level characteristics. The binary fixed effect for the intervention will estimate the expected within-site change in the co-primary outcomes associated with the intervention.

Associations between the dependent variable and fixed effects will be modelled using the logit link function. An identity link function will also be fitted as a comparison, to report risk differences. If the identity link function does not allow the model to converge, results for the logit link function will only be reported. Results for both unadjusted (except clustering) and adjusted analyses will be reported. Model parameters will be reported as estimated ORs (risk differences) with 95% CIs.

Subgroup analyses for the co-primary outcomes will examine intervention effects by sex, surgical specialty, type of anaesthesia, duration of surgery, elective/emergency, ASA classification I–V. A sensitivity analysis will also consider hypothermia defined at the following thresholds: <36°C, <35.5°C and <35°C.

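### A plain Poisson mixed model for units of blood transfused gives intervals that are too narrow if patients who are transfused commonly receive more than one unit

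*Protocol article*

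**What the plan says.** Table 1 (Outcome measures, row 7) gives the measure for blood product transfusions as "Number of units transfused in surgery and PACU". This is a secondary effectiveness outcome.

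The Secondary analysis section says "Secondary outcomes will be similarly modelled based on the form of the dependent variable", then "Binary and count outcomes will be modelled using binomial and Poisson GLMMs, respectively", and then "Models for count outcomes will assume a common denominator of cases per 1000 surgeries".

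The structure carried over comes from the Primary analysis section: "A random intercept will be defined for each site to account for clustering of observations under the stepped wedge design". The fixed effects are intervention exposure, calendar time in months and patient-level or surgery-level characteristics. Unadjusted and adjusted results are both to be reported. The article names no dispersion term and no patient-level random effect.

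**The concern.** A Poisson model sets the variance equal to the mean, given the terms in the model. Blood is given in units, and a patient who needs it may receive several in one episode. If so, the variance of units per patient is a multiple of the mean. That excess lies between patients within a site, so five site intercepts cannot pick it up. The standard error of the intervention effect is then too small.

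The Introduction lists transfusion among the reported harms of hypothermia. An interval that is too narrow could therefore support a claim of benefit or harm on this outcome that the data do not justify. Both the outcome and the model are stated in the article, so this concerns what the plan fixes, not what it leaves out.

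**Working it through.** **Inputs.** From the article: units as the outcome (Table 1), Poisson with a site intercept (Secondary and Primary analysis), and a 5% significance level (Sample size determination and power, stated there for the primary outcome; two-sided is assumed here). The article gives no transfusion rate, units per patient, dispersion or power for this outcome, so there is no figure of its own to reproduce. Everything about transfusion below is an assumption.

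**Formula.** Let a share p of patients be transfused, and let those patients receive a mean of m units with variance v. Units per patient then have mean pm and variance p(v + m²) − p²m². So

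- variance/mean: φ = (v + m²)/m − pm, which is at least m(1 − p);
- Poisson SE divided by true SE: 1/√φ;
- true error rate of a nominal 5% test: 2 × [1 − Φ(1.96/√φ)].

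Example with p = 2%, m = 2, v = 1: φ = 5/2 − 0.04 = 2.46; 1/√2.46 = 0.64; 1.96 × 0.64 = 1.25; error rate about 21%.

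**Results for p from 1% to 5%.**

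| Units if transfused | φ | SE ratio | True error rate |
|---|---|---|---|
| exactly 1 | 0.95–0.99 | 1.01–1.03 | 4–5% |
| mean 1.5, v = 0.5 | 1.76–1.82 | 0.74–0.75 | 14–15% |
| mean 2, v = 0 to 2 | 1.90–2.98 | 0.58–0.73 | 16–26% |
| mean 3, v = 2 to 4 | 3.52–4.30 | 0.48–0.53 | 30–35% |

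The first row shows that zeros alone do no harm: a rare yes/no event has φ of about 1. The cause is several units going to one patient.

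**Check by simulation with no intervention effect.** The Randomisation section gives control starts in months 1, 1, 1, 4 and 7, a 6-month transition, and 6 to 18 months of intervention. With 3-month steps, (18 − 6)/4, inferred from that range, this makes 3 + 6 + 9 + 9 + 9 = 36 control and 18 + 15 + 12 + 9 + 6 = 60 intervention site-months. Monthly samples were set at 59, 100, 140, 175 and 226 patients. The two ends are stated in the article and the middle three are assumed. The total is 12,819, inside the stated range of 12,732 to 14,100. The model was Poisson with site effects (fixed, standing in for the random intercept), time and intervention. Units among those transfused were 1 plus a Poisson variable.

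- Linear time, p = 2% and 5%, 600 runs each: rejection 5.2% and 6.2% at one unit each; 15.2% and 14.8% at mean 1.5; 20.2% and 18.8% at mean 2; 30.3% and 31.7% at mean 3.
- Month as a category, p = 3%, mean 2, 400 runs: 24.0%.
- Same data, SEs scaled by the Pearson dispersion: 3.5% to 6.3% where the mean exceeds one unit (linear time), and 6.5% with month as a category.
- Same data, counting transfused patients instead of units: 3.7% to 6.2% across all settings.

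Monte Carlo error at a true 5% is about √(0.05 × 0.95/600) = 0.9 percentage points for 600 runs and 1.1 for 400. The corrected analyses are therefore close to nominal, and the inflation under plain Poisson is well beyond simulation noise.

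**The case against.** The strongest reply is that the article may not mean to model units at all. Its denominator sentence speaks of cases. If transfused patients are counted, the outcome is a rare yes/no event and Poisson standard errors are close to correct, as the last simulation line shows. This stands as an ambiguity, but not as a defence: Table 1 says units, and changing the denominator of a count of units does not change its dispersion. One of the two statements has to give way.

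Second, nothing in the article says how blood is given at these sites. If nearly every transfused patient receives one unit, there is no inflation. This stands, and the conclusion is conditional for that reason.

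Third, covariates may absorb part of the excess variance, and an analysis plan that is not shown may add a dispersion check. Both are possible. Covariates cannot help the unadjusted result, and they would have to predict very well who is transfused to remove the excess from the adjusted one. A fallback elsewhere would settle the point, but the model named in the article is plain Poisson.

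A reader might also infer that the same fault affects complications in theatre or PACU. Table 1 does not say whether these are counted or recorded as yes/no, and yes/no outcomes go to the binomial model. A reader might further infer that the economic results are affected. Units transfused are not a listed economic input, and the Cost-effectiveness analysis section takes its uncertainty from bootstrapping individual costs and QALYs, not from this model.

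**Conclusion.** The point holds conditionally. If units are analysed and transfusions of more than one unit are common, the stated model gives standard errors roughly 0.6 to 0.7 of their true size at a mean of 2 units and about half at a mean of 3. Error rates are then three to seven times nominal (16/5 to 35/5). At one unit each there is no inflation. All of this assumes 1% to 5% of patients transfused, the unit distributions shown, and no dispersion correction elsewhere.

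It would go too far to say that false-positive transfusion effects are likely. Even at the top of the range, about 65% of tests under no effect would still not reject. It would also go too far to state as fact that most patients receive none and the rest several units, or to blame the zeros. The impact is confined to one secondary outcome.

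**What to change.** In the Secondary analysis section, for units transfused, replace the plain Poisson mixed model by a negative binomial mixed model, or by Poisson with standard errors scaled by the patient-level dispersion. Keep the same site, time and intervention terms. Only the scaled version was tested in the full simulation. A shorter run of 150 replicates gave 1.3% rejection for the negative binomial, which suggests it may be conservative, so a brief check before choosing is worthwhile.

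In the same edit, state whether the outcome is units, as in Table 1, or transfused cases, as the denominator sentence suggests. If cases are meant, amend Table 1 and analyse any transfusion with the binomial mixed model already specified. If units are meant, express the rate as units per 1000 surgeries. Making any transfusion the main result is not needed to cure the defect while units remain the defined outcome.

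The cost is a sentence or two, no new data, and wider intervals: by √φ, about 1.3 times at a mean of 1.5 units, 1.4 to 1.7 at a mean of 2, and 1.9 to 2.1 at a mean of 3.

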## Introduction

 Perioperative systems of care are not designed to keep patients warm. General and neuraxial anaesthesia impairs thermoregulation, meaning heat loss is inevitable without warming.^1^ Patients have limited control over exposure to cold ambient conditions and their thermal comfort. Body temperature is not consistently monitored throughout perioperative care.^2^ Most temperature monitoring and warming occur after surgery is complete^2^ and after patients have already been exposed to the complications of hypothermia.^2 3^ Warming practices are often not proactive or consistently based on patient needs.^2^ Indeed, pre-emptive and coordinated hypothermia prevention practices may be constrained in a system where competing priorities include patient flow and productivity.^4^

The discomfort of perioperative hypothermia and associated shivering is remembered by patients well after surgery.^1^ The potential adverse outcomes reported in the literature are wide-ranging, including increased wound infection,^5^,^7^ risk of surgical bleeding^8^ and blood transfusions,^5^ myocardial injury and morbid cardiac events,^8 9^ delays in drug metabolism,^1^ prolonged post-anaesthetic recovery times and hospital stays.^7 10^ The cost of perioperative hypothermia to the healthcare system is an estimated $A1.2 billion per annum.^11^ Prevention would produce an estimated net cost-benefit of $A689 659 per annum for an average size healthcare facility, due to the prevention of hypothermia-related morbidity.^12^

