#### Consensus-based simple principles and recommendations

Using a consensus-based process reported previously in this journal,^18^ the evidence-based simple principles and accompanying detailed recommendations for hypothermia prevention, were adapted for the Australian context. The three principles for perioperative hypothermia prevention are (1) actively monitor core temperature for all patients at all times, (2) warm actively to keep temperature above 36°C and patients comfortable and (3) minimise exposure to cold at all stages of perioperative care.^18^ These represent the three main strands of hypothermia prevention, providing a guide to action with the support of detailed recommendations where needed. Rather than trying to enforce compliance with detailed guidelines, working with principles is compatible with our tailored implementation approach.^12 19^

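### Any-time hypothermia (secondary outcome 2) rises with the number of temperatures recorded, which the intervention aims to increase, so the comparison is biased against the intervention; calling missing outcomes low does not fit the 2.7% monitoring figure

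*Protocol article*

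**What the plan says.** All references are to the protocol article.

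- **Outcome measures, Table 1, outcome 2.** "Perioperative hypothermia at any time point" means a temperature below 36°C in any of five windows: the hour before surgery, induction, intraoperative, PACU stay, and readiness for PACU discharge. No minimum number of readings is set.
- **Secondary analysis.** "Missing data on primary and secondary outcomes is expected to be low". The imputation rule there is for covariates: "In the event of missing data on patient-level covariates, missingness will be investigated and if missing at random variables will be imputed using multiple imputation". The section also promises to report levels of missing data.
- **Sample size determination and power.** The implementation calculation starts from "Assuming that 2.7% of patients currently receive temperature monitoring at all recommended time points" and aims to "detect an increase from 0.027 (2.7%) in the control period to 0.1 (10%) in the intervention period with 82% power".
- **Introduction.** On usual care: "Body temperature is not consistently monitored throughout perioperative care". The same paragraph adds that most monitoring takes place after surgery.
- **Consensus-based simple principles and recommendations.** The first principle is to "actively monitor core temperature for all patients at all times". Under Implementation outcomes, the extent of temperature monitoring is part of the co-primary implementation outcome.
- **Primary analysis.** The model has a random intercept per site and fixed effects for exposure, calendar month and patient or surgery characteristics. Secondary binary outcomes are modelled in the same way.

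**The concern.** Outcome 2 is a union over recorded readings. A patient measured once has one chance to be found below 36°C, and a patient measured in all five windows has at least five. The intervention is meant to raise the number of windows recorded, so ascertainment differs between periods by design.

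The model cannot separate this from a change in patients' temperatures. The change in recording coincides with exposure, so neither the site intercept nor calendar month absorbs it.

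The trial could therefore succeed on monitoring, keep patients warmer, and still report a much reduced fall in any-time hypothermia. The expectation of low missingness gives readers no warning of this.

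**Working it through.** **1. The plan's own figures.** The plan puts no number on missing temperatures, so there is none to reproduce. Its monitoring figures imply:

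- control: 100 − 2.7 = 97.3% lack a reading at one or more recommended time points;
- intervention at the planned target: 100 − 10 = 90%.

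These are not exact missingness rates for outcome 2. The recommended time points come from a cited study, and Table 1 audits four monitoring stages against the outcome's five windows. They are still hard to square with low missingness for an outcome built from readings at those stages.

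**2. Requiring complete readings is not a way out.** The Randomisation section gives clusters 1–3 a control start in month 1, clusters 4 and 5 starts in months 4 and 7, a 6-month transition, and 6 to 18 months of intervention. Assuming 3-month steps over 27 months:

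- control months: 3 + 6 + 9 + 9 + 9 = 36;
- intervention months: 18 + 15 + 12 + 9 + 6 = 60;
- control share: 36/96 = 0.375, if sites were of equal size.

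Fully measured control patients: 12,732 × 0.375 × 0.027 ≈ 129, to 14,100 × 0.375 × 0.027 ≈ 143. With half the sample in control it would be 172 to 190.

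**3. Direction.** Let c be the chance that a window is recorded and p the true risk in that window. If windows were independent and unrecorded windows counted as normal:

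P(recorded any-time hypothermia) = 1 − ∏(1 − c·p).

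This increases in every c. The direction does not need independence, because adding a reading to a union cannot remove a case.

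**4. Size, by hand, in the limiting case of independent windows.** Assumed risks are 10, 20, 27.4, 27.4 and 10%, with recording equal across windows.

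- Control: c = 0.027^(1/5) = 0.486, so 1 − 0.9514² × 0.9029 × 0.8669² = 38.6%.
- Intervention, no true change: c = 0.10^(1/5) = 0.631, so 1 − 0.9369² × 0.8738 × 0.8271² = 47.5%.

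The spurious rise is about 9 points. Temperatures within a patient are correlated, which makes it smaller.

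**5. Size, with correlation.** Latent-normal simulation, five windows, 400,000 patients per scenario, the same risks, within-patient correlation 0.3 to 0.8, complete monitoring rising from 2.7% to 10%:

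| Recording pattern | No true effect: recorded change | True fall of about 9 to 11 points: recorded fall |
|---|---|---|
| Equal across windows | rise of about 4 to 7 points | about 2 to 4 points |
| PACU already recorded in 97% | rise of about 2 to 4 points | about 6 points |

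The second row is closer to the Introduction's remark that most monitoring follows surgery. Risks, correlations and recording patterns are all assumptions.

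**The case against.** **Much of this may belong in the analysis plan.** The article does not say how unrecorded windows are handled, and such rules are commonly left to a plan that is not shown here. That is fair, and the absence of a rule is not the point. The point is that the definition, followed as printed, gives a result that depends on recording, and that a stated expectation conflicts with a stated figure.

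**The authors partly acknowledge it.** They note their reliance on complete records, promise to report missing data, and audit monitoring by stage under outcome 12. This stands, and it makes the fix cheap. But nothing says that the intervention itself changes completeness, or that coverage will be set beside outcome 2 by period.

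**The bias is conservative.** Under the natural reading it cannot create a false claim of benefit on this outcome. That stands and limits the severity.

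**A reader might infer that the primary outcome is biased in the same way.** The documents do not support this. The primary outcome uses one 15-minute window, so it is not a union over windows. The 2.7% concerns all recommended points together and says nothing about recording on PACU arrival, and the Introduction places most monitoring after surgery. Even with substantial missingness the direction would be open. Suppose recording of 85% then 97% and a true change from 0.274 to 0.200, that is −7.4 points. Counting unrecorded patients as normal gives 0.97 × 0.200 − 0.85 × 0.274 = −3.9 points. Analysing measured patients only, with every cold patient measured, gives 0.200/0.97 − 0.274/0.85 = −11.6 points. Those recording rates are invented for illustration.

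**A reader might also infer that a true benefit would be reversed.** At the planned change from 2.7% to 10%, no scenario in the table does so. Reversal appeared only in some scenarios with complete monitoring at 50%, a figure the protocol does not contain.

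**Conclusion.** The point holds for secondary outcome 2. Its direction, against the intervention, follows from the definition provided that unrecorded windows count as not hypothermic. Its size is not fixed by the documents. A spurious rise of about 2 to 7 points at the planned monitoring change is illustrative and rests on the assumed window risks, correlations and recording patterns. The expectation of low missing data is inconsistent with the 2.7% figure for this outcome. It is not shown to be wrong for the primary outcome or for the other secondary outcomes. Should be fixed; it does not threaten the primary effectiveness comparison.

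**What to change.** 1. Limit the statement on low missing data to outcomes other than any-time hypothermia.
2. Make hypothermia in each window, among patients measured in that window, the main presentation of outcome 2, with recording coverage by window and period alongside. Who gets measured may still differ between periods, and coverage makes that visible.
3. Keep the any-time composite but label it as dependent on ascertainment. Add a sensitivity analysis adjusted for, or restricted to, comparable recording. Imputing unrecorded windows is an alternative, but it would fill gaps for most control patients under a missing-at-random assumption that is open to doubt, so it should not be the main analysis.
4. For the primary outcome, report the proportion with a qualifying PACU-arrival reading by period, as a check only.

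Settle this before outcome data are analysed, since the Blinding section says the trial statistician cannot be blinded. The cost is some extra analysis, largely of data already extracted or audited under outcome 12, and somewhat wider intervals. Recruitment, sampling and care do not change.
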